## Abstract

Supplemental Digital Content is available in the text

## Introduction

1

Chronic obstructive pulmonary disease (COPD) constitutes a group of diseases including small airway obstruction, emphysema, and chronic bronchitis. Chronic inflammation of the airway and lung parenchyma is the main feature of this disease, with progressive and irreversible airflow limitation.^[1]^ The main clinical manifestations are repeated cough, sputum, and dyspnea. It is usually caused by abnormal airways and alveoli caused by significant exposure to toxic particles or gases. The latest Global Initiative for Chronic Obstructive Lung Disease (GOLD) 2019 guidelines have added risk factors for COPD, such as indoor biofuels, socioeconomic status, human immunodeficiency virus infection, and genetic polymorphisms.^[2]^ Acute exacerbation of COPD (AECOPD) is defined as a sudden worsening of the main complaint (baseline dyspnea, cough, or sputum) in patients with COPD that exceeds normal day to day variations. Currently, the prevalence of COPD is on the rise. It is expected that more than 4.5 million people will die annually owing to COPD by 2030. Thus, COPD will become the third leading cause of death worldwide and a public health problem in every country.^[3,4]^

Airway inflammation is the most basic pathological change in COPD, especially in the acute exacerbation stage,^[5]^ which formed the theoretical foundation for glucocorticoid therapy. The systemic use of glucocorticoids, one of the major treatments for AECOPD,^[6]^ promotes symptom relief, shortens the course of AECOPD, reduces the length of hospital stay, and improves forced expiratory volume in 1 s (FEV1) values; however, the long-term use of steroid hormones causes muscle weakness, diabetes, osteoporosis, fluid retention, hypertension, adrenal depression,^[7]^ secondary infections (pneumocystis pneumoniae), seizures, insomnia, weight gain, anxiety, depressive symptoms, and many other significant adverse reactions.^[8]^ Each side effect is an independent risk factor for death.^[9]^ Therefore, clinicians are actively seeking safer alternative treatments that still benefit from the use of glucocorticoids.

Treatment with syndrome differentiation is one of the characteristics of the traditional Chinese medicine (TCM) theoretical system, and it is advantageous in the treatment of COPD and has achieved significant effects. “Phlegm-heat congested lung” is one of the major features of COPD.^[10]^ The TCM for clearing heat and resolving phlegm often achieves good effects in the treatment of AECOPD,^[11]^ inhibits inflammatory reactions,^[12]^ reduces airway mucus hypersecretion,^[13]^ controls lung infection, and reduces the use of antibacterial drugs.^[14]^ Based on these effects, we intend to further study the heat-clearing and phlegm-resolving effects of TCM on the reduction of the dosage of systemic glucocorticoids. In this trial, the dosage of systemic glucocorticoids will be regarded as the primary endpoint. The secondary endpoints will include: symptom scores, assessed by the COPD assessment test (CAT) scores and modified medical research council dyspnea scale scores (mMRC); exercise tolerance, measured by 6 minute walking distance (6MWD); lung function, measured by forced expiratory volume in 1 second (FEV1), the ratio of forced expiratory volume in 1 second to forced vital capacity (FEV1/FVC), and FEV1 as a percentage of predicted value (FEV1%); inflammatory indicators, include C-reactive protein (CRP) and procalcitonin (PCT); length of hospital stay; and symptoms and quality of life scores during the follow-up. The efficacy of TCM in the treatment of AECOPD will be assessed by these indicators.

## Methods

2

### Trial design and oversight

2.1

This will be a prospective, placebo-controlled clinical trial to evaluate the efficacy of TCM in the treatment of patients with AECOPD. A total of 204 eligible patients will be enrolled according to the exclusion and inclusion criteria and randomly assigned to the TCM or placebo group at a 1:1 ratio. The antibiotic group and non-antibiotic group will be set in advance for subgroup analysis. After a 7–14 day intervention and 12 weeks of follow up, the efficacy of TCM in the treatment of patients with AECOPD will be evaluated based on the primary endpoint (the dosage of systemic glucocorticoids [at which CAT scores improve by 50%]) and secondary endpoints (symptoms scores, exercise tolerance, lung function, length of hospital stay, symptoms, and quality of life scores during the follow up). The flow chart of the study is presented in Figure 1.

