### Randomization and intervention

2.6

The randomization protocol will be designed by a member of the Sichuan TCM Evidenced-Based Medicine Center. They will generate 204 random numbers will using SAS 9.2 statistical software (SAS Institute, Cary, NC). Treatment allocation will be conducted by an independent statistician according to the random numbers generated by the statistical software. Eligible patients will be randomly assigned to either the TCM group or the placebo group using sealed opaque envelops after obtaining informed consent. A special manager will record this randomization process. An individual's randomization number and group allocation can be identified by checking the envelope, which will be performed in case of a clinical emergency.

All participants will receive basic Western medical therapy advocated by the Chinese Expert Consensus on the diagnosis and treatment of AECOPD (2017 update),^[8]^ which includes:

1.Controlled oxygen therapy: Venturi mask inhales oxygen.2.Bronchodilators: compound ipratropium bromide solution for inhalation (Laboratoire Unither, Amiens, France), 2.5 mL, inhale, three times a day;3.Phlegm medicine: fudosteine tablets (Pharmaceutical Co., Ltd.), 0.4 mg, orally, three times a day;4.Glucocorticoids: methylprednisolone sodium succinate for injection (Tianjing Jinyao Pharmaceutical Co., Ltd. Tianjing, China), 40 mg, administered with 0.9% sodium chloride injection (100 mL), intravenously, once a day (depending on the patient's condition, the dosage can be reduced or changed to oral administration, but the longest course of treatment cannot exceed 14 days);5.Antibacterial drugs: according to bacterial resistance and the general course of treatment will be 5 to 7 days, although special circumstances can appropriately extend the application time of antibacterial drugs.

In addition, the TCM group will receive TCM granules (one bag at a time, three times a day) and the Placebo group will receive Placebo granules (one bag at a time, three times a day). Both groups will or will not receive antibiotic treatment according to the antibiotic treatment criteria, which are:

1.During AECOPD, aggravated difficulty breathing, increased sputum volume, and purulent sputum occur simultaneously;2.The patient only has two of the above three symptoms, but has purulent sputum;3.Severe acute exacerbation that requires invasive or noninvasive mechanical ventilation.

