### Prespecified subgroup analysis

2.12

A subgroup analysis will be performed on the use of antibiotics and no antibiotics in the TCM and placebo groups to explore the correlation between antibiotic therapy and the outcomes of the study.

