One of the advantages of this test is that it facilitates the observation of the reduction of glucocorticoid dosage as the main outcome indicator. The dosage of glucocorticoids can be adjusted by changing the CAT score, which has guiding significance for regulating the use of clinical glucocorticoids. Secondly, this trial pre-sets a subgroup analysis based on the need for antibiotic treatment, which is in line with the clinical practice of antibiotic use. The shortcomings of this trial are that the TCM intervention time for AECOPD patients is short, which may affect the expected results, as prolonging the patient's treatment time with TCM may be beneficial to patient condition and prognosis. However, the results of this study are only applicable to a single AECOPD patient group with phlegm-heat congested lung syndrome. It will still be unknown whether patients who do not meet this syndrome can be effectively treated using the same TCM. A final disadvantage is that samples will be gathered from a single center only, which will reduce the applicability and generalizability of the results.

The purpose of this test is to observe whether the TCM for clearing heat and resolving phlegm can reduce the dosage of glucocorticoids in hospitalized patients and provide more evidence for the treatment of AECOPD by TCM.

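### The antibiotic subgroup is defined three ways (set in advance, by use, by need) with no time point, so grouping by actual use could let treatment decide who is in it

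*Protocol article*

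**What the plan says.** The protocol article describes its only prespecified subgroup in several places.

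- **Trial design and oversight (2.1):** "The antibiotic group and non-antibiotic group will be set in advance for subgroup analysis".
- **Randomization and intervention (2.6):** "Both groups will or will not receive antibiotic treatment according to the antibiotic treatment criteria". Two of the three criteria combine presenting symptoms (worse dyspnoea, more sputum, purulent sputum). The third is "Severe acute exacerbation that requires invasive or noninvasive mechanical ventilation". No time point is given for applying them. The same section also lists antibacterial drugs within the basic therapy that every participant is to receive.
- **Prespecified subgroup analysis (2.12):** "A subgroup analysis will be performed on the use of antibiotics and no antibiotics in the TCM and placebo groups".
- **Discussion (3):** "this trial pre-sets a subgroup analysis based on the need for antibiotic treatment", presented as a strength of the trial.

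On allocation, section 2.6 says: "Eligible patients will be randomly assigned to either the TCM group or the placebo group using sealed opaque envelops after obtaining informed consent". Study procedures (2.14) places consent and baseline data collection before the randomised treatment.

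**The concern.** A subgroup in which a treatment effect is estimated should be fixed by information that exists before randomisation. Arms compared within it then differ only by chance. Whether the antibiotic criteria are met at entry is such a factor. Whether antibiotics are actually given during a stay of 7 to 14 days is not, because treatment can change it.

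The article itself supplies the reason to worry. Its Introduction says that TCM of the heat-clearing, phlegm-resolving kind helps control lung infection and cuts the use of antibacterials. If so, some TCM patients who would have had antibiotics on placebo go without. The TCM and placebo patients within each subgroup are then no longer alike at baseline. Antibiotic use probably goes with severity, and severity with steroid dose, so the within-subgroup contrast in the primary endpoint would mix treatment effect with selection. At stake is the interpretation of the one subgroup analysis that the trial prespecifies.

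**Working it through.** **Step 1: the definitions side by side.**

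| Section | Basis of the subgroup | Can it be known before the envelope is opened? |
|---|---|---|
| 2.1 | Set in advance | Not clear: may mean only that the analysis is prespecified |
| 2.12 | Use of antibiotics | No, if use over the stay is meant |
| Discussion | Need for antibiotics | Yes, if scored at entry |
| 2.6 | Criteria met, no time stated | Symptom criteria yes; ventilation in part |

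On ventilation, section 2.4 excludes patients who need invasive mechanical ventilation, while the third antibiotic criterion includes them. An enrolled patient can therefore meet the invasive part only after entry. At least one route into the antibiotic group thus opens after randomisation.

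**Step 2: how large could the distortion be?** The plan gives no figure for this subgroup, so there is none to reproduce. The following is an illustration on assumptions.

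- From section 2.5: SDs of 31.1 and 32.9 mg, pooled SD = √((31.1² + 32.9²)/2) = 32.01 mg; planned difference 256.7 − 187.6 = 69.1 mg. They are used only as a scale.
- Assumed: no true TCM effect on dose; dose proportional to a normal severity score with SD 32.01 mg; antibiotics given when a normal score correlated ρ with severity exceeds a threshold; antibiotics do not themselves alter dose; ρ = 0.3 to 0.5; use 10 percentage points lower under TCM.

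With a share p using antibiotics and φ the normal density at the threshold, mean dose relative to the arm mean is 32.01·ρ·φ/p in users and −32.01·ρ·φ/(1 − p) in non-users. The values of φ are 0.1755 (p = 0.9), 0.2800 (0.8), 0.3477 (0.7) and 0.3863 (0.6).

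Example, use 90% on placebo and 80% on TCM:
- users: 0.2800/0.8 − 0.1755/0.9 = 0.155; × 32.01 × 0.5 = 2.48 mg
- non-users: 0.1755/0.1 − 0.2800/0.2 = 0.355; × 32.01 × 0.5 = 5.7 mg

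False TCM minus placebo difference (mg):

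| Use, placebo → TCM | Users, ρ = 0.3 | Users, ρ = 0.5 | Non-users, ρ = 0.3 | Non-users, ρ = 0.5 |
|---|---|---|---|---|
| 70% → 60% | 1.41 | 2.36 | 1.85 | 3.09 |
| 80% → 70% | 1.41 | 2.35 | 2.31 | 3.85 |
| 90% → 80% | 1.49 | 2.48 | 3.41 | 5.69 |

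Simulation of the same model agrees to about 0.1 mg. All entries are positive: TCM looks worse in both subgroups although the overall difference is zero. The patients who move are milder than the remaining users and sicker than the other non-users, so both TCM means rise. With equal use in both arms every entry is zero.

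**Step 3: scale.** 1.4/69.1 = 2% and 5.7/69.1 = 8% of the planned difference. The distortion is small, but it is systematic and does not shrink with more patients.

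**The case against.** **The subgroup may in fact be a baseline one.** The Discussion speaks of need, two of the three criteria are mostly presenting features, both arms follow the same criteria, and baseline data precede treatment. All of this stands. A post-randomisation definition is therefore possible, not stated. What remains is that section 2.12, the section that specifies the analysis, says use, and an analyst who follows it would group by use.

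**Use is the natural variable for the stated aim.** Section 2.12 wants to explore how antibiotic therapy relates to outcomes, and 2.16 compares the two subgroups with each other. For that question, use is a reasonable exposure. But it is then a non-randomised association, and it does not justify reading the TCM effect within groups formed by use.

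**The analysis is exploratory and the illustrated bias small.** Both are true, and they limit the weight of the point.

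**A stronger reading.** From "They will generate 204 random numbers will using SAS 9.2 statistical software", a reader might infer a single unstratified list and conclude that the subgroups will be badly unbalanced between arms. The document does not support this. 204 is simply the total sample, which is "randomly assigned to the TCM or placebo group at a 1:1 ratio"; that fits a stratified list as well as a simple one. The article is condensed, and its flow chart is not shown. Nor would an unstratified list be an error: chance imbalance in a factor fixed at baseline does not bias the comparison, and even a 40:60 split keeps 4 × 0.4 × 0.6 = 96% of the efficiency of an even one. That the non-antibiotic group will be small is also unsupported: no share is given, and the sputum sign required at entry is not equated with the purulent sputum in the antibiotic criteria.

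**Conclusion.** The point holds as an inconsistency of definition with a plausible route to bias. The basis of the subgroup differs between sections 2.1 and 2.12 and the Discussion, and 2.6 gives no time for applying the criteria. If actual use is taken, the within-subgroup comparison of TCM and placebo conditions on something that, by the article's own rationale, treatment may change.

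The size is modest: about 1.4 to 2.5 mg among users and 1.9 to 5.7 mg among non-users. These figures rest on an assumed severity model, an assumed 10-point drop in use and assumed shares of 60% to 90%; none of these comes from the document. The overall randomised comparison is not affected. Nothing here shows that randomisation is unstratified or that stratification is required. This is a minor, easily made improvement.

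**What to change.** 1. Record, before the envelope is opened, whether the patient meets the existing antibiotic criteria.
2. Define the subgroup in section 2.12 by that baseline status in place of later use, and bring 2.1 and the Discussion into line with it.
3. If the association of actual antibiotic use with outcome is still of interest, report it separately and label it non-randomised.
4. Reconcile two further pairs of statements: antibacterials listed in basic therapy for all against antibiotics given by criteria (both in 2.6), and the ventilation criterion in 2.6 against the exclusion in 2.4.

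Optionally, use the baseline status as a covariate in the primary analysis. Stratifying randomisation by it is also optional and corrects no error.

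The cost is about one case report form field and a few sentences of text. The small downside is that the criteria must be scored before allocation. Who receives antibiotics does not change.

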**Figure 1 F1:**
[figure not shown]
Flow chart of the study design. TCM = traditional Chinese medicine, WBT = western basic therapy.

This trial has been registered in the Chinese Clinical Trial Registry (ChiCTR) (ChiCTR2000029568) on February 5, 2020 and approved by the China Ethics Committee of Registering Clinical Trials (Approval No. ChiECRCT20200022). The main test center will be the Affiliated Hospital of Chengdu University of Traditional Chinese Medicine. This trial will be conducted in accordance with the Declaration of Helsinki (Edinburgh 08 version) and the Recommendations for Interventional Trials of the Standard Protocol Items (SPIRIT) initiative 2013 (see Supplemental Digital Content)^[15]^; all patients will need to provide written informed consent to proceed. If there is any amendment to the protocol, approval must be again sought from the Ethics Committee. Trial data will be uploaded to the ChiCTR within the prescribed period and published in the form of a paper in an international or domestic peer-reviewed journal.

### Participants

2.2

This trial will begin to recruit 204 cases in June 2020. All the participants will be recruited from the inpatient department of the Respiratory Department of the Affiliated Hospital of Chengdu University of Traditional Chinese Medicine.

The western medicine diagnosis of AECOPD is similar to that of the Chinese Expert Consensus on the diagnosis and treatment of AECOPD (2017 update).^[8]^ Patients often show exacerbation of shortness of breath, often accompanied by wheezing, chest tightness, coughing, increased sputum volume, sputum color and viscosity changes, and fever. In addition, non-specific symptoms, such as tachycardia, shortness of breath, general malaise, insomnia, drowsiness, fatigue, depression, and mental disorders, may occur. Reduced exercise tolerance, fever, and chest imaging abnormalities may be clinical signs COPD.

The syndrome differentiation of “Phlegm-heat congested lung” refers to the 2012 Guidelines for Diagnosis and Treatment of COPD (2012).^[16]^ Primary symptoms include cough, wheezing, tightness in the chest, excessive phlegm production, yellow and white sticky sputum, white sticky dryness in the throat, increased expectoration, red tongue with yellow and greasy tongue coating, and a slippery or rapid pulse. Secondary symptoms include chest pain, fever, thirst for cold drinks, dry stool, and thick tongue coating. The diagnosis of phlegm-heat congested lung is based on:

1.cough or shortness of breath;2.polychromatic, yellow, and white sticky sputum;3.fever and thirst for cold drinks;4.dry stool; and5.red, yellow, or yellow greasy tongue, and a slippery or rapid pulse.

The diagnosis should meet (1) and (2) and two of (3), (4), and (5).

### Inclusion criteria

2.3

Patients who meet the diagnosis of phlegm-heat congested lung syndrome of AECOPD and need systemic glucocorticoid administration;COPD GOLD stage 3 or 4 (post-bronchodilator forced FEV1/FVC < 70% and FEV1 < 50% of predicted);Age from 40 to 65 years old and have symptomatic COPD (CAT scores ≥ 10), regardless of sex;No history of allergies to the drugs used in the experiment;Expected survival time ≥30 days;Patients and their families agree to participate and sign informed consent.

### Exclusion criteria

2.4

Atypical bacterial infections, such as atypical pathogens and drug-resistant bacteria;Complicated with a severe tumor, unstable coronary heart disease, abnormal liver and kidney function, cerebrovascular accident, and other diseases;Other associated active or clinically significant respiratory diseases that have a significant impact on the study, such as active pulmonary tuberculosis, lung cancer, bronchiectasis, pulmonary hypertension, pulmonary interstitial disease, and other active lung diseases;Severe hypertension, diabetes, peptic ulcer, and other glucocorticoids contraindications;Patients who require invasive mechanical ventilation;Pregnant, lactating, and menstrual women;Patients with mental disorders who are unable to actively cooperate with treatment;Patients with a history of allergies to related drugs.

### Sample size

2.5

Based on the primary endpoint (the dosage of systemic glucocorticoids) to calculate sample size. According to a previous study,^[17]^ the dosage of systemic glucocorticoids during the hospitalization of patients with AECOPD with TCM is 187.6 ± 31.1 mg (methylprednisolone sodium succinate for injection) and that with western medicine treatment is 256.7 ± 32.9 mg. Using a formula, we will set α = 0.05 and β = 0.2 and hope that 80% power can be used to uncover the true difference between the treatment options. According to the formula, nc = (μ1−α / 2 + μ1−β) ^2^S^2^ (1 + 1 / k) / (μt-μc) 2 = 87. Thus, the control group requires 87 cases. According to the 1:1 ratio, a total of 174 cases are needed in the two groups. Considering a possible dropout rate of 15%, a total of 174/0.85 = 204 cases are required, with 102 cases in each group.

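### The 87 patients per group do not follow from the formula and inputs printed in Section 2.5, which give 4 per group, so the stated basis for 174/204 patients and 80% power is wrong

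*Protocol article*

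**What the plan says.** Section 2.5 (Sample size) sizes the trial on the primary endpoint: "Based on the primary endpoint (the dosage of systemic glucocorticoids) to calculate sample size". Citing a previous study, it reports that "the dosage of systemic glucocorticoids during the hospitalization of patients with AECOPD with TCM is 187.6 ± 31.1 mg" and "that with western medicine treatment is 256.7 ± 32.9 mg". The error rates are given as "we will set α = 0.05 and β = 0.2", and the aim is expressed as a "hope that 80% power can be used to uncover the true difference between the treatment options".

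The section then prints a formula for the control-group size. It is the squared sum of the two normal quantiles, times S squared, times (1 + 1/k), divided by the squared difference in means, and it is set equal to 87. The conclusion is "Thus, the control group requires 87 cases". Doubling for 1:1 allocation gives 174, and a 15% dropout allowance leads to "a total of 174/0.85 = 204 cases are required, with 102 cases in each group".

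Section 2.16 (Statistical analysis) says that tests are two-sided at the 5% level, which agrees with the 1−α/2 quantile in the formula. The section gives no other difference, SD, margin or adjustment.

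**The concern.** The quoted difference is more than twice the quoted SD. A standardised difference of that size needs only a handful of patients per group, so 87 looks wrong on sight.

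The sample size section should let a reader connect three things: the effect planned for, the variability assumed, and the number enrolled. If the number does not follow from the inputs, the stated 80% power does not describe this design. A reader then cannot tell whether the inputs, the target or the arithmetic is at fault. The possible explanations describe quite different trials: one able to detect about 14 mg, or one with an SD about five times the quoted value.

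**Working it through.** **Inputs (Section 2.5, with sidedness also from Section 2.16)**
- Means 187.6 and 256.7 mg; difference 256.7 − 187.6 = 69.1 mg.
- SDs 31.1 and 32.9 mg; pooled S = √[(31.1² + 32.9²)/2] = √1024.81 = 32.01 mg.
- Standardised difference 69.1/32.01 = 2.16.
- Two-sided alpha 0.05 and beta 0.2: 1.960 + 0.842 = 2.802, squared 7.85.
- k = 1, so (1 + 1/k) = 2.

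**Attempt to reproduce 87.** n = 7.85 × S² × 2 / 69.1², with 69.1² = 4774.81.
- S = 31.1: n = 3.18
- S = 32.01: n = 3.37
- S = 32.9: n = 3.56

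Each rounds up to 4 per group. With an exact t-test and the pooled SD, power is about 72% at 4 per group and 85% at 5, so 5 is the smallest size that reaches 80%. The stated 87 is about 22 times the formula's answer (87/4).

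**Other readings tried.** S is not defined in the section, and the superscripts are poorly rendered in the text, so other readings were checked.
- S as the root of the summed variances (45.27): 6.7, so 7.
- S as the sum of the two SDs (64.0): 13.5, so 14. Raising power to 99% as well gives 32, the largest value found from the formula across one- and two-sided tests and powers from 80% to 99%.
- An efficiency adjustment for the Wilcoxon test: 3.5 to 3.9.
- Denominator read as the difference times 2 instead of squared: 110 (S = 31.1), 116 (pooled S) or 123 (S = 32.9).
- Denominator left unsquared: 233 with pooled S.

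None of these gives 87.

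**What 87 per group delivers**
- For 69.1 mg at S = 32.01, the standard error of the difference is 32.01 × √(2/87) = 4.85 mg. Then 69.1/4.85 = 14.2, far beyond 1.96, and power is above 99.99%.
- The difference detectable with 80% power is 2.802 × 32.01 × √(2/87) = 13.6 mg by the normal approximation and 13.7 mg by the t distribution. The standardised difference is 0.42 and 0.43 respectively.
- The SD at which 69.1 mg has 80% power is 69.1/0.4248 = 162.7 mg by the normal approximation and 161.8 mg by the t distribution. That is about five times 32.01.

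**Later steps.** 2 × 87 = 174 is correct. 174/0.85 = 204.7, printed as 204; 204 × 0.85 = 173.4. This is a rounding matter only.

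**The case against.** The best defence is that nothing is lost. The section names a planning difference, and 87 per group detects it with near certainty. A null result could be judged against 69.1 mg, and a confidence interval would remain interpretable. This stands, and it limits the point: the error lies in the justification and the stated power, not in a shortage of patients. A reader might infer from a failed sample size calculation that the trial is too small. The document does not support that, because on its own inputs the error runs the other way.

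A reader might also infer that the quoted SDs are suspect, because at 40 mg a day the quoted means equal only 4.7 and 6.4 days (187.6/40 and 256.7/40) while the stay is 7 to 14 days. That does not follow. Sections 2.7 and 2.14 give 7 to 14 days as the hospital stay and intervention period, not as the steroid course. Section 2.6 sets only a 14-day maximum for the steroid and lets the dose be reduced or changed to oral. Sections 2.1 and 2.10 define the endpoint as the dose at which the CAT score has improved by 50%, which can be reached before discharge. The cited means are compatible with this, and a mismatch in means would in any case not show that an SD is wrong.

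Finally, it is tempting to assume that another SD lies behind 87. That cannot be established. As conjecture only, leaving both the quantile sum and the difference unsquared with S = 32.9 gives 2 × 2.80 × 32.9²/69.1 ≈ 87.7. That is not the printed formula, but it shows that 87 could be an arithmetic slip with no hidden assumption to report.

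**Conclusion.** The point holds. From the printed formula and inputs, the requirement is 4 per group (5 by exact t-test), against the stated 87. The 80% power attached to 87 is also wrong for the quoted difference and SDs, where power is essentially 100%. Both figures support the sample size for the primary endpoint, so they need correcting.

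The result rests only on numbers in Section 2.5, on reading the ± values as SDs, and on the two-sided test in Section 2.16. It does not depend on which of the printed SDs is taken as S. How 87 arose cannot be recovered from the document.

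The finding does not extend to inadequate power, to doubt about the cited SDs, or to a claim that no planning difference is stated. The rounding of 204.7 to 204 is trivial: the shortfall is 174 − 173.4 = 0.6 of an evaluable patient.

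**What to change.** Keep the enrolment of 204 and correct Section 2.5:

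- Delete the statement that 87 follows from the cited means and SDs.
- Then do one of two things. Either disclose the difference and SD that produce 87, with their source. Or state that the calculation was in error and report what 87 evaluable patients per arm provide: 80% power for a standardised difference of about 0.43, which is about 13.7 mg at the quoted SD, and power above 99.99% for 69.1 mg. On the second route, present these figures as the properties of the chosen size, not as a target fixed in advance.
- Define S in the formula.
- As a minor correction, print 174/0.85 as 204.7 and note that 204 leaves about 173 evaluable patients at 15% dropout.

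The cost is protocol wording, plus the ethics committee approval that Section 2.1 requires for any amendment. Enrolment, treatment and analysis do not change.
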